### Adverse events

Because all studied tests concern usual care and a previous cohort study among older patients (mean age 78.5 years) who received similar tests did not result in any adverse events,^27^ we consider the risk classification of this study as ‘negligible risk’. This was confirmed by the Medical Ethical Review Committee (METC). All adverse events that occur during the study, whether or not considered related, will be recorded. Serious adverse events (SAEs) will be reported to the accredited METC that approved the protocol, within 7 days of first knowledge for SAEs that result in death or are life-threatening followed by a period of maximum of 8 days to complete the initial preliminary report. All other SAEs will be reported within a period of maximum of 15 days.

### Data collection

During a home visit, the study physician will conduct data collection in which patient characteristics, history taking and physical examination are recorded in a standardised manner using the electronic case report form within the online Castor Electronic Database environment.^45^ Castor is a computer-assisted interviewing system and survey processing tool that will help to create a standardised setting and to avoid missing data. The study’s electronic case report form in Castor is programmed in such a way that it is capable of detecting alarming findings (so-called ‘red flags’) after all index tests are recorded and summarise these at the end of a home visit. In the case of missing data, these results will be imputed.

### Statistical analysis

#### Primary analysis: regression analysis and receiver operating characteristic (ROC) analysis

For each target condition, we will measure the amount of agreement between the outcome of (individual and combinations of) index tests and the consensus diagnosis. We will construct 2×2 tables to calculate sensitivity, specificity, prior probabilities, positive and negative predictive values, positive and negative likelihood ratios, and diagnostic ORs. Subsequently, we will perform multivariable logistic regression analysis with ‘presence or absence of target condition X, according to consensus diagnosis’ as dependent variable. Prior to multivariable regression analysis, we will perform univariate logistic regression analysis to investigate the associations between separate diagnostic indicators and the dependent variable. Variables will only be entered in the multivariable regression model if the univariate p value is <0.15. During multivariable analysis, we will follow the chronology in which investigations are performed in daily clinical practice.^46^ First, we will include all findings from history taking. This model will be reduced by (one by one) excluding variables with a likelihood p value of >0.10. Subsequently, we will add the results of physical examination (and possible other additional diagnostic tests) to quantify their added diagnostic value. Again, we will use a p value of >0.10 as cut-off to construct the final models. For each of the five target conditions (ie, (1) BPPV, (2) vestibular neuritis, (3) Ménière’s disease, (4) VM and (5) central causes other than VM), we will construct a final model and calculate sensitivity, specificity, predictive values, likelihood ratios, and diagnostic ORs.

After multivariable regression, in order to distinguish the discriminative ability (ie, the ability to discriminate patients with target condition X from patients without this target condition), an ROC curve will be constructed out for each target condition. An area under the curve (AUC) of 0.5 indicates no discrimination, whereas an AUC of 1.0 indicates perfect discrimination.^46^ We will test continuous variables for linear association with the outcome and we will use Spearman’s rank correlation coefficient to investigate multicollinearity.

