## Methods and analysis

### Aims and objectives

The main objective is to investigate the diagnostic accuracy of history taking and physical examination for patients with vertigo of primary vestibular origin in general practice.

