#### Reference standard

During this study, we will compare each index test with its respective reference standard. Researchers investigating the diagnostic accuracy of a test often encounter ‘no gold standard situations’: situations where the reference standard is not available for all patients, where the reference standard is imperfect or where there is no accepted reference standard.

Consensus or panel diagnosis, an example of a constructed reference standard, is an attractive alternative if a generally accepted reference standard does not exist and multiple sources of information have to be interpreted to reach a diagnosis. In a consensus diagnosis, a group of experts determines the presence or absence of the target condition in each patient based on multiple sources of information. These sources can include general patient characteristics, signs and symptoms from history and physical examination, and other test results.^24^

We will focus on five target conditions that account for more than 95% of vertigo diagnoses in general practice: (1) BPPV, (2) vestibular neuritis, (3) Ménière’s disease, (4) VM and (5) central causes of vertigo.^7^ As these five target conditions have a different pathophysiology and all lack a generally accepted reference standard, we will use consensus diagnosis as reference standard. Data for each patient, including history, physical examination and additional tests as recommended by international guidelines,^1 11 25 29 31 32^ will be recorded on a standardised form within Castor (see the Data collection section) and independently reviewed by a neurologist and otorhinolaryngologist. In case of disagreement, a third reviewer (neurologist or otorhinolaryngologist) will be invited to reach consensus. The reviewers will not meet, in order to avoid domination.^24^

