#### Additional testing

Depending on the history taking and physical examination by the study physician during the home visit, a subset of patients may report symptoms that imply a medical indication for additional testing.

Patients with vertigo accompanied by hearing loss, tinnitus and/or aural fullness will receive pure-tone audiometry within 4 weeks after the home visit.

Patients with daily, non-episodic vertigo lasting over 14 days and substantial dizziness-related impairment (defined as a DHI-S score of ≥12)^33^ will receive state-of-the-art videonystagmography (VNG) within 4 weeks after the home visit.^36–40^ Additionally, patients indicated to undergo the HINTS Plus exam will also undergo VNG.

Prior to receiving VNG, patients will undergo a video Head Impulse Test, the Dix-Hallpike test using Frenzel glasses and the Supine Roll test using Frenzel glasses. During VNG, the function of the vestibular organ will be investigated during several test situations, that is, spontaneous nystagmus, oculomotor examination, rotational testing and caloric testing. The total testing time is about 60–90 min.

It is estimated that around 10% of patients will receive audiometry while around 30% of patients will receive VNG based on additional analyses of the general practice cohort within the DIEP (Dizziness In Elderly Patients study) study.^27^

When a patient displays a ‘red flag’, the study physician will contact the patient’s GP the same day. The study physician will advise the GP to act in accordance with the Dizziness Guideline of the Dutch College of GPs (see table 2), which implies that a patient with a red flag may receive additional testing after being referred. To get a complete testing overview, we will approach the patient’s GP to collect these additional data.

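### The final-model step admits additional tests such as audiometry and VNG together with physical examination, although they lie outside the objective and inform the panel diagnosis

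*Protocol article*

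**What the plan says.** All references are to the protocol article.

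- **Aims and objectives.** The purpose of the study is given as follows: "investigate the diagnostic accuracy of history taking and physical examination for patients with vertigo of primary vestibular origin in general practice".
- **Index tests, Table 3.** The table that lists all index tests contains history and physical examination items. It contains neither audiometry nor VNG.
- **Additional testing.** Audiometry is triggered by ear symptoms. VNG is triggered either by long-lasting daily vertigo with a high handicap score or by an indication for the HINTS Plus exam. Both take place within 4 weeks after the home visit, and the article expects that "around 10% of patients will receive audiometry while around 30% of patients will receive VNG". The VNG appointment also includes a video head impulse test and repeats the Dix-Hallpike and supine roll tests.
- **Reference standard.** The panel reviews "Data for each patient, including history, physical examination and additional tests as recommended by international guidelines".
- **Primary analysis.** The dependent variable is the panel's consensus diagnosis. History is modelled and reduced first. Then "we will add the results of physical examination (and possible other additional diagnostic tests) to quantify their added diagnostic value". Then: "Again, we will use a p value of >0.10 as cut-off to construct the final models". One final model per target condition results.
- **Data collection.** "In the case of missing data, these results will be imputed".

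**The concern.** The modelling step is wider than the objective it serves. It allows tests that are not index tests to enter at the same moment as physical examination and to survive into the only final model named for each condition.

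Three things are at stake if the option is used.

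1. The step is meant to measure added diagnostic value. When examination and later tests enter together, the increment due to examination, which is half of the objective, cannot be read off. An examination item may also be eliminated because a later test replaces it. This is a concrete risk, because the VNG appointment repeats two manoeuvres that are themselves index tests.
2. The additional tests are part of the information that determines the outcome. The Introduction criticises earlier Dix-Hallpike evidence for exactly this incorporation bias. The Discussion concedes that the panel depends on the index tests but says nothing about the additional tests. Overlap with index tests is hard to avoid with a panel; this further overlap is optional.
3. The results feed an algorithm for GPs. A final model with a VNG or audiometry term relies on a result obtained up to 4 weeks after the home visit.

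**Working it through.** **Step 1: does the parenthesis refer to audiometry and VNG?** The analysis section names no test. In the Home visit section, the case report form lists the indicated additional diagnostic tests once the index tests have been entered. The Additional testing section then describes audiometry, VNG and tests after referral. That is the article's own use of the term, so the reading is well supported, though not explicit.

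**Step 2: does joint entry fit the plan's own modelling rule?** The analysis is to follow the order of investigations in daily practice. Tests done up to 4 weeks after the home visit come later than the examination, so a single step for both does not follow that order.

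**Step 3: how many patients would have a result?** Inputs: 960 patients (Sample size) and shares of 10% and 30% (Additional testing, planning estimates from a cohort of older patients).

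| Test | With result | Without result |
|---|---|---|
| Audiometry | 0.10 × 960 = 96 | 960 − 96 = 864 |
| VNG | 0.30 × 960 = 288 | 960 − 288 = 672 |

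Central causes at 5% give 0.05 × 960 = 48 cases overall. If they were equally frequent among tested patients (an assumption, since triggers select patients), there would be 0.05 × 96 = 4.8 and 0.05 × 288 = 14.4 cases with a result.

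**Step 4: which way does incorporation push the estimates?** The documents give no panel weights, so this can only be illustrated. Assumptions: 10% prevalence; 400,000 simulated patients; testing triggered by history in 10% or 30%; a panel score that gives the test result a weight of 0 to 1.5; logistic models with an indicator for having been tested. Without the test, the AUC is 0.846 against true disease and 0.927 to 0.950 against the panel.

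| Test | Panel weight | Odds ratio, truth | Odds ratio, panel | AUC gain, truth | AUC gain, panel |
|---|---|---|---|---|---|
| No true value | 0 | about 1.0 | about 1.0 | 0.000 | 0.000 |
| No true value | 0.5 to 1.5 | about 1.0 | 2.1 to 9.9 | 0.000 | 0.002 to 0.039 |
| Real value, 30% tested | 0.5 | 2.2 | 3.1 | 0.015 | 0.011 |
| Real value, 30% tested | 1.0 | 2.2 | 6.5 | 0.015 | 0.026 |
| Real value, 30% tested | 1.5 | 2.2 | 14.1 | 0.015 | 0.042 |

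The row with weight 0 is the control: a worthless test stays worthless until the panel uses it. The odds ratio rises whenever the panel gives the test weight. The AUC gain can go either way, because the model without the test also looks better against the panel.

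**Step 5: a second illustration.** Assumptions: vestibular neuritis at 41%, clinical AUC of about 0.80, VNG in the 30% with the highest suspicion, VNG sensitivity 0.80 and specificity 0.85.

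- Against truth, the AUC gain is 0.839 − 0.802 = 0.037.
- Against a panel that follows VNG in 70% of tested patients, it is 0.936 − 0.894 = 0.042.
- Against a panel that follows VNG in 90%, it is 0.955 − 0.877 = 0.078.

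At 70% the two gains hardly differ; at 90% the gain roughly doubles.

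**The case against.** The best defence is that the text is permissive. It says possible, names no test, and the same section opens with agreement between index tests and the panel. Final candidate predictors are commonly fixed in an analysis plan, which is not at hand. The staged design also limits the damage: a history-only model is built first, and the 2×2 accuracy of each index test does not depend on this step. Asking what further testing adds is a fair question. Losing a term at the 0.10 cut-off can happen with any correlated predictor, including examination findings.

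Much of this stands, and it rules out three stronger readings that a reader might infer.

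- **That added value will certainly be inflated.** Steps 4 and 5 show that the AUC gain may be nearly unchanged or even smaller against the panel. The size depends on panel behaviour that the documents do not describe.
- **That the GP model will be unusable.** This needs a test to be entered, to pass univariate selection, to be retained, and then to be carried into the algorithm, which is built in a later phase. Nothing says that every term must be carried over.
- **That tests never indicated will be imputed.** The imputation sentence closes a paragraph on home-visit data. Extending it to audiometry and VNG is an inference. The simulations use a tested indicator and so do not measure any such harm.

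The defence does not remove the mismatch. The parenthesis is wider than the objective and the index test list, and it is attached to the step that produces the only final models named.

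**Conclusion.** The point holds as a conditional one. As written, the primary analysis permits tests outside the objective, done on triggers in an estimated 10% and 30% of patients and known to the panel, to enter with physical examination and remain in the final model. If that happens, the examination's added value is not isolated, the odds ratios of these tests may be inflated, and the resulting model would be hard to apply at a GP consultation.

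The counts (864 and 672 of 960 without a result) rest on the article's planning estimates. The odds ratios of 2.1 to 9.9 for a worthless test rest on assumed panel weights and show direction rather than expected size. The inconsistency between objective and modelling step depends on neither. It does rest on reading the parenthesis in the sense in which the article uses additional tests elsewhere. I rate this as a cheap improvement.

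**What to change.** Delete the parenthesis from the sentence on adding physical examination, so that the primary final models end at history plus physical examination. State that audiometry, VNG and tests obtained after referral serve as panel input. If their added value is of interest, report it as a separate exploratory step in tested patients, with the panel's knowledge of the results stated as a limitation, and do not use it as the basis of a GP decision rule. Add that a test not indicated is not missing data and is not imputed.

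The cost is a sentence or two in the analysis section. No patient, visit, test or change in sample size is involved. The one downside is that the reported AUC of the final models may be slightly lower.

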#### Secondary analysis: reliability and validation

In order to assess the reliability of the model, we will calculate the Hosmer-Lemeshow goodness-of-fit statistic and construct calibration plots.^47^ Because diagnostic models perform better in development cohorts than in other similar populations (overfitting), we will perform a bootstrapping procedure. During this procedure, we will repeat the entire modelling process, in order to validate the final models and to adjust (shrink) the estimated performance and regression coefficients.^48^

As empirical research has shown that variability among raters influences diagnostic accuracy,^49^ we will calculate the inter-rater reliability (ie, the reliability across multiple reviewers) and intrarater reliability (ie, the reliability of a single reviewer) by calculating Cohen’s kappa. Kappa values less than 0.00 indicate poor, 0.00–0.20 slight, 0.21–0.40 fair, 0.41–0.60 moderate, 0.61–0.80 substantial and greater than 0.81 almost perfect agreement.^50^

### Data availability statement

Data from the VERDI study will be made available in the future for collaborative research questions. Such requests must be authorised by the principal investigators and the appropriate METC.

### Patient and public involvement

Patients play a crucial role during the realisation, execution and knowledge dissemination of the VERDI study. In 2020, we used the input of patients with vertigo during the writing of the research proposal. Additionally, we used the input of the Dutch patient organisation Stichting Hoormij·NVVS on diagnosing vertigo in general practice.

During the execution of the VERDI study, a patient representative of the Committee Dizziness And Balance/Hoormij·NVVS will be a permanent member of the research group in order to represent the perspective of patients with vertigo. During the interim evaluations of the VERDI study, we will ask patients from our general practice network and the patient organisation Hoormij·NVVS to provide input in order to identify possible obstacles and suggest adjustments if necessary.

Finally, we will collaborate with the patient organisation Stichting Hoormij·NVVS to successfully disseminate the results of the VERDI study to patients with vertigo.

## Discussion

### Diagnostic accuracy study

The GP’s diagnostic toolkit for vertigo is limited since recommended tests lack empirical evidence, primarily because a diagnostic accuracy study on vestibular disease has never been performed in general practice. This diagnostic accuracy study will fill this scientific gap by providing concrete accuracy measures for individual and combined signs, symptoms and diagnostic tests in adults presenting with vertigo in general practice. From a more clinical perspective, the results of our regression analyses with respect to each target condition will provide valuable insight into which clinical tests offer the largest diagnostic contribution for each specific target condition, and also which tests—based on negligible diagnostic contributions—are perhaps superfluous in vertigo diagnosis in general practice.

A possible limitation of the study is that our constructed reference standard, that is, the consensus diagnosis by a panel of experts, is dependent on results of index tests collected during the home visit by study physicians. In order to mitigate this possible limitation, all study physicians have substantial clinical expertise and will receive a 3-hour training aimed at correct execution, interpretation and documentation of the index tests. We deliberately chose not to have medical specialists carry out the index tests, since this may negatively affect the generalisability of our findings for general practice.^51^

### Following steps for the VERDI project

After this diagnostic accuracy study (phase III) has ended, the next step of VERDI will be to use the results of this study to construct a diagnostic algorithm (phase IV) in order to enable GPs to more accurately and efficiently identify underlying causes in patients with vertigo. Improvement of the current situation is crucial, because GPs on the one hand are responsible for the treatment of 80% of the patients,^7–9^ while on the other hand they are often (36–40%) not able to provide a diagnosis.^8 26^

As clinical decision rules may have limited effect on physicians—due to the perception of diminished autonomy, the conviction that clinical judgement is superior, weak incentives for using the decision rule consistently or the concern that important factors are not addressed by the decision rule^52^—it is crucial to demonstrate that a decision rule has additional value to the clinical judgement of the GP.

Using the results of a diagnostic accuracy study in order to construct a decision rule for use in clinical practice is a major scientific project which is not risk-free. Failing to convincingly demonstrate the additional value of such a clinical decision rule for GPs would result in a limited impact on clinical practice.

In phase IV of the VERDI study, we will conduct semistructured interviews with a small sample of patients and practising GPs in order to investigate barriers and facilitators for successful implementation of the decision rules and the corresponding diagnostic strategy. In the final phase of the VERDI study (phase V), we will compare the diagnostic accuracy of GP judgement with the accuracy of the constructed diagnostic algorithm.

If proven accurate, our diagnostic algorithm may lead to faster and more targeted treatment, less diagnostic imaging and referral, less prescribing of antivertigo drugs and improvement of the overall outcome for patients with vertigo in general practice. With faster and more accurate diagnoses, patients can often be treated in general practice and expensive additional testing and referral to secondary/tertiary care can be avoided.

The proposed study therefore has the potential to reduce both the enormous personal burden of vertigo and its associated economic burden (total annual economic burden in the USA is US$48.1 billion, US$13.3 billion directly attributed to vertigo/dizziness).^53^ From a wider perspective, the results of this study may contribute to further reinforcement of primary care. According to the late Barbara Starfield, this can relieve the burden on secondary/tertiary care, leading to better care at lower costs.^54^

### Ethics and dissemination

The study obtained approval from the Vrije Universiteit Medical Center Medical Ethical Review Committee (reference: 2022.0817—NL83111.029.22). We aim to widely disseminate the insights and results of this project to patients, GPs, GP trainees, physiotherapists, elderly care physicians, GP organisations and patient associations. For this purpose, we will publish the results in international peer-reviewed journals and disseminate our results by means of (national and international) conference presentations.
